### Intervention(s)

The Disease Management Model is based on 3 elements: coordination of care, guiding of the care process and empowerment of the patient [10]. A limitation of disease management for patients with multi-morbidity is the single-disease oriented perspective. Therefore in this project among elderly with mostly multiple morbidity, we choose an expanded multidimensional or biopsychosocial perspective which corresponds to the International Classification of Functioning, Disability and Health [24]. For our target population we defined disease management as improving or maintaining the functional health status by providing continuity of care, being patient oriented, generating multidimensional health data on residents, executed by appropriately trained professionals who design a shared disease management plan and is ICT supported.

In the intervention homes we will make disease management operational in the process of care in three sequential steps: 1. Firstly a three-monthly in-home systematic and computerized multidimensional assessment of all residents by staff (nurse) who systematically identifies the functional health status and care needs. For this purpose, the inter RAI LTCF instrument will be used [25].

The Resident Assessment Instrument (RAI) was originally designed as a minimum data set to assess the health needs of nursing home residents. For the homes for the elderly we use the inter RAI LTCF (Long Term Care Facility) version. The interRAI LTCF provides a comprehensive overview of the person's physical, psychological, behavioral and social status. Moreover it indicates a global level of care need which distinguishes persons who do not need care, from those who need personal care, home care, extramural home care or nursing home care. The computerized interRAI LTCF produces an easy and direct overview of problems in 18 areas that may need specific care planning. The identified problem areas guide the design of an optimal individualized care plan. In a multidisciplinary team, all disciplines involved in care for the resident, will participate in regular meetings in order to evaluate the interRAI LTCF findings and design and monitor the (tailor made) care-plan. The care plan aims to improve or maintain the functional health status and is focused at modifiable risk factors of the resident (Table 2).

**Table 2 T2:** Case example RAI-LTCF assessment by nurse: triggered modifiable health risks

Problems and risks	Observed	Action now?

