### Economic evaluation

Cost data are collected by resident interview at base line, and at 6 months from a societal perspective and supplemented with resource use as registered within the home for the elderly. In case residents are cognitively impaired or not able anymore to be interviewed, proxies will be sought, preferably close family members. Only direct healthcare costs will be considered, because all patients have retired. Included cost categories are costs of consultations with the general practitioner, the nursing home physician and medical specialists, hospitalizations and admissions to the medical department of the nursing home and use of medication and medical aid. Medication data are retrieved from the centralized pharmacy files in the research region. Care consumption will be valued according to guidelines for economic evaluation in health care in the Netherlands [36,37].

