## Discussion

In this paper we described the design of a randomized cost-effective trial of the effect of Disease management on residents of homes for the elderly. This study holds several unique elements. The intervention concerns continuity of care and identification of care needs of the residents. The use of interRAI LTCF enables nurses to accurately diagnose the problems addressed within the complex clinical status of a frail elderly person. As a consequence, primary care physicians will be better informed about the health problems of their patients. This may enable effective disease management. Finally, to persons with complex problems a multidisciplinary consultation is offered by a nursing home physician.

The randomization on level of the homes for the elderly may be a weak point of the design as specific cultural habits of the homes will not be equally distributed over the two groups. On the other hand, randomization of homes will prevent contamination of the intervention to usual care homes.

The implementation of interRAI LTCF demands a great effort on the part of the organization and outcomes are dependent on good use of the instrument.

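### The listed cost categories leave out programme-specific intervention costs, and the societal label does not match the direct healthcare costs that are counted

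*Protocol article*

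**What the plan says.** The Economic evaluation section of the protocol article first states the perspective and the sources: "Cost data are collected by resident interview at base line, and at 6 months from a societal perspective", "supplemented with resource use as registered within the home for the elderly". It then narrows the scope: "Only direct healthcare costs will be considered, because all patients have retired". The categories follow: "Included cost categories are costs of consultations with the general practitioner, the nursing home physician and medical specialists", and after these "hospitalizations and admissions to the medical department of the nursing home and use of medication and medical aid". Table 1 has a single economic row, direct costs, drawn from patient or family interview, pharmacy registration and medical records.

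The Cost analysis and Cost effectiveness analysis sections use the resulting totals. The difference in mean costs gets a bootstrap interval (2000 replicates). The difference in total costs is set against functional health, disability and QALYs. Bootstrapped cost-effect pairs (5000 replicates) feed the cost-effectiveness plane and the acceptability curves.

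The Abstract and the Intervention(s) section describe what the intervention homes do: train staff, have a nurse assess every resident each quarter on a computerized LTCF, discuss the results in a multidisciplinary meeting, and offer the frailest residents a consultation. The Discussion says of this: "The implementation of interRAI LTCF demands a great effort on the part of the organization".

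**The concern.** An economic comparison of a care programme with usual care has to include what the programme costs to run. Most of the resources that define this programme do not appear in the list. If the list is followed as written, savings that the programme produces elsewhere (fewer admissions, less medication) would be counted, while much of the spending that produced them would not. A programme that raises costs could then be reported as saving them. Economic effects are part of the study's stated objective, so this would affect a headline conclusion.

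A second, separate problem is the label. A reader of a societal evaluation expects family care and residents' own expenses to be included. The reason given for leaving out everything but direct healthcare costs is retirement, and that reason does not reach those items.

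**Working it through.** The article gives no figure for intervention cost, so there is nothing to reproduce. The check is a comparison of texts, followed by the algebra of the omission.

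**Step 1: intervention resources against the cost list.**

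| Resource (where described) | In the list in Economic evaluation? |
|---|---|
| Staff training (Abstract) | No |
| Computerized LTCF system (Abstract, Intervention(s)) | No |
| Nurse time for three-monthly assessments (Intervention(s), step 1) | No |
| Multidisciplinary meeting time of physicians, nurse and psychotherapist (step 2) | No, not as meeting time |
| Psychotherapist consultation (Abstract, element 3) | No |
| Nursing home physician consultation (Abstract, element 3) | Yes |
| GP consultation | Yes |

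Five items are unlisted. The sources in Table 1 do not obviously supply them either.

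**Step 2: effect on the cost difference.** Let C be the mean uncosted programme cost per intervention resident, with C > 0. The programme is defined only for the intervention homes, so the matching amount in usual care is zero.

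- Reported cost difference = true cost difference − C.

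**Step 3: effect on the ratio.** Let ΔQ be the QALY gain.

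- Reported ICER = (true cost difference − C) / ΔQ = true ICER − C/ΔQ, for ΔQ > 0.
- At any willingness to pay λ, net benefit is λΔQ − cost difference. Omitting C raises it by C whatever λ is, so the whole acceptability curve moves toward the intervention.
- Bootstrapping does not help, because programme cost is missing from every replicate.

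**Step 4: illustration.** All inputs here are assumptions. With linear interpolation, as the Cost effectiveness analysis section specifies, equal baselines and a utility difference of 0.05 at 6 months, ΔQ = 0.05 × 0.5 years × 0.5 = 0.0125.

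| Assumed C (EUR) | ΔQ = 0.01 | ΔQ = 0.0125 | ΔQ = 0.05 |
|---|---|---|---|
| 100 | 10,000 | 8,000 | 2,000 |
| 500 | 50,000 | 40,000 | 10,000 |

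Entries are C/ΔQ, the amount in EUR per QALY by which the ICER would be too low. The spread, 2,000 to 50,000, shows how strongly the result depends on two unknown inputs.

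**Step 5: the perspective.** The section says costs are collected "at 6 months from a societal perspective" and then limits them to direct healthcare. Retirement explains why residents have no lost paid work. It does not explain leaving out unpaid care by family or expenses paid by residents and families. Those could be higher or lower under the intervention, so the sign of this second omission is not known.

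**The case against.** The strongest reply is that programme costing may be intended but not spelled out. The section adds resource use registered in the home, which could hold nurse time and meetings. Nurse and meeting time are direct healthcare costs, so the restriction to direct healthcare does not exclude them. The list might describe only residents' care consumption, with programme cost handled in a fuller document under the cited costing guidelines. Part of this stands: the home's records may capture some staff time. But their content is undefined, and the article does not merely stay silent. It states which categories are included, and the programme items are not among them.

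A reader might also infer four stronger things that the article does not support:

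- That nothing the intervention adds is costed. Nursing home physician and GP consultations are listed.
- That both defects favour the intervention. Only the missing programme cost has a known direction.
- That the remark in the Discussion about great effort shows a large cost. It describes organisational effort and gives no amount.
- That the forms kept for the process evaluation already hold the needed data. That section describes performance against protocol, recommendations, compliance and professionals' judgments; it does not mention time or cost.

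Finally, the perspective restriction is disclosed next to the label, so a careful reader can see what is counted. That limits the harm but does not remove the contradiction.

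**Conclusion.** The point holds in two parts.

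First, the list as written omits the programme-specific costs of the intervention. A cost difference built from it is too low for the intervention arm by the uncosted amount per resident, and for a positive QALY gain the ICER is too low by that amount divided by the gain. This assumes that the list is applied literally and that the home's own records do not already supply these items; whatever they do supply reduces C. The size cannot be derived from the article, and the EUR figures above are illustration, not evidence of magnitude.

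Second, the societal label is wrong for an analysis confined to direct healthcare costs. The resulting bias has no known direction.

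Only the cost side of the economic evaluation is affected. The clinical effect analyses and the sample size calculation are untouched.

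**What to change.** - Add an intervention cost category to the list in Economic evaluation and to Table 1: staff training, LTCF software, nurse assessment time, multidisciplinary meeting time of each discipline, and psychotherapist consultations.
- State that nursing home physician and GP consultations already listed are not counted again under this category.
- Name the data source: the home's records, if they hold staff time, or a time field added to the process registration forms.
- Call the perspective healthcare throughout. Alternatively, keep societal and add informal care and out-of-pocket items to the existing resident or family interview. Relabelling alone is not enough, because programme costs belong in a healthcare perspective too.

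The price is a little extra recording, a few interview items if the societal perspective is kept, and an economic result less favourable to the intervention than the current list would give.

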**Methods:**

This study concerns a cluster randomized controlled clinical trial among five intervention homes and five usual care homes in the North-West of the Netherlands with a total of over 500 residents. All persons who are not terminally ill, are able to be interviewed and sign informed consent are included. For cognitively impaired persons family proxies will be approached to provide outcome information. The Disease Management Model consists of several elements: (1) Trained staff carries out a multidimensional assessment of the patients functional health and care needs with the interRAI Long Term Care Facilities instrument (LTCF). Computerization of the LTCF produces immediate identification of problem areas and thereby guides individualized care planning. (2) The assessment outcomes are discussed in a Multidisciplinary Meeting (MM) with the nurse, primary care physician, nursing home physician and Psychotherapist and if necessary other members of the care team. The MM presents individualized care plans to manage or treat modifiable disabilities and risk factors. (3) Consultation by an nursing home physician and psychotherapist is offered to the frailest residents at risk for nursing home admission (according to the interRAI LTCF). Outcome measures are Quality of Care indicators (LTCF based), Quality Adjusted Life Years (Euroqol), Functional health (SF12, COOP-WONCA), Disability (GARS), Patients care satisfaction (QUOTE), hospital and nursing home days and mortality, health care utilization and costs.

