Delirium		
Cognition impairment /dementia		
Visual impairment	x	
Communication	x	
ADL-revalidation potential	x	x
IADL-more formal care needed		
Urinal incontinence	x	
Psychosocial wellbeing	x	x
Depression	x	
Behavior		
Social activities	x	
Falls	x	x
Nutrition	x	
Artificial nutrition		
Dehydration		
Dental health		
Skin problems and wounds	x	x
Psychotropic medication-walking problems		
Psychotropic medication- cognitive and behavioral problems		
Psycho medicaments and feeling unwell		
Fixation		

2. Secondly, the assessment outcomes are discussed in a multidisciplinary meeting (MM) in the homes with the primary care physician, nursing home physician, nurse, Psychotherapist and other involved disciplines. In the MM an individualized care plan is made to treat modifiable disabilities and identify and eliminate (when possible) risk factors.

3. Thirdly, a multidisciplinary consultation is offered to the frailest residents with complex health care problems. They are identified by the level of expected resource utilization [26].

In addition, the computerized interRAI LTCF also provides process-supporting information technology as well as indicators about the functioning and implementation of the care plans.

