### Process evaluation

The process evaluation involves assessing the extent to which the intervention program is performed according to protocols, the nature of the recommendations made to the participants of the MM, compliance with these recommendations, physicians and therapists judgments about the intervention program and recommendations. Data on these topics are collected using structured registration forms during the intervention. Finally, semi-structured interviews will be held with the participating nurses, primary care physicians, and nursing home physicians at the end of the intervention period in order to record their experiences and opinions on the new disease management model.

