#### Cost effectiveness analysis

For the cost-effectiveness analysis the difference in total costs between the intervention and usual care group are compared with the difference over 6 months in improvement of functional health and disability. In addition, a cost utility analysis will be done to assess the incremental costs per Quality Adjusted Life Years (QALY). QALY's are calculated by multiplying the utility based on EuroQol scores [29] with the amount of time a patient spent in this particular health state. Transitions between health states are linearly interpolated.

Uncertainty around the cost-effectiveness and cost-utility ratios is calculated using the bias-corrected percentile method (5000 replications) and presented in a cost-effectiveness plan [39]. The bootstrapped cost and effect pairs will also be used to calculate cost-effectiveness acceptability curves [40].

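### The listed cost categories leave out therapist and allied-health contacts, although a psychotherapist is part of the model being costed

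*Protocol article*

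**What the plan says.** The Economic evaluation section sets a societal perspective, with data collected at baseline and "at 6 months from a societal perspective and supplemented with resource use as registered within the home for the elderly". It then narrows the scope: "Only direct healthcare costs will be considered, because all patients have retired". The categories follow as a plain list: "Included cost categories are costs of consultations with the general practitioner, the nursing home physician and medical specialists", then "hospitalizations and admissions to the medical department of the nursing home and use of medication and medical aid". Nothing in that sentence marks the list as a set of examples.

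The intervention is described in two places. The Methods part of the abstract gives the third element of the model: "Consultation by an nursing home physician and psychotherapist is offered to the frailest residents at risk for nursing home admission". In the Intervention(s) section, step 2 has the assessment discussed by the primary care physician, nursing home physician, nurse, psychotherapist and other disciplines concerned, and continues: "In the MM an individualized care plan is made to treat modifiable disabilities and identify and eliminate (when possible) risk factors". The case example in Table 2 flags rehabilitation potential in daily activities, psychosocial wellbeing, falls and skin problems for immediate action.

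The Cost effectiveness analysis section sets "the difference in total costs between the intervention and usual care group" against changes in functional health and disability. It adds a cost-utility analysis per QALY, bootstrapped uncertainty and acceptability curves.

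**The concern.** The cost list and the intervention do not match. Two professionals are named together as giving consultations to the frailest residents; the consultations of one are costed and those of the other are not. The other disciplines in the planning meeting have no cost category either, unless they happen to be medical specialists.

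At stake is the numerator of every cost-effectiveness result. Where therapist or allied-health care improves function, disability or utility, the gain is counted on the effect side. If the cost of that care is left out and its use differs between arms, the cost difference, the ratios and the acceptability curves are all shifted. Resampling cannot repair this: neither the 2000 replications for costs nor the 5000 for the ratios can restore a category that was never recorded.

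**Working it through.** The article contains no cost figure to reproduce. The check is therefore a comparison of the cost list with the intervention, followed by the algebra of the omission.

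**Step 1. Components against cost list.**

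| Component | Role in the model | In the cost list? |
|---|---|---|
| Primary care physician | planning meeting (Intervention(s), step 2) | yes |
| Nursing home physician | planning meeting; consultation for the frailest (abstract) | yes |
| Psychotherapist | planning meeting; consultation for the frailest (abstract) | no |
| Other disciplines | planning meeting (step 2) | only if medical specialists |
| Admissions, medication, aids | possible consequences of a care plan | yes |

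**Step 2. Does the stated scope explain the gap?** The scope is direct healthcare costs, and the reason given is that residents are retired. Retirement is a reason to leave out lost work. It is no reason to leave out treatment by a therapist, which is a direct healthcare cost. The scope therefore does not account for the omission.

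**Step 3. Effect on the result.** Let D be the difference in mean cost per resident (intervention minus usual care) over the listed categories. Let m₁ and m₀ be the mean numbers of therapist and allied-health contacts per resident in the two arms, and p the unit price.

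- Full difference = D + A, where A = (m₁ − m₀) × p.
- Reported difference = D, so the error is −A.
- With a QALY difference E, the cost-utility ratio is shifted by A / E.

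If m₁ > m₀, the reported result is too favourable to the intervention. If m₁ = m₀ there is no bias, and if m₁ < m₀ the bias runs the other way. The article states neither m₁ nor m₀, nor an expectation for them.

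**Step 4. How it scales (assumptions only).** None of these inputs is in the article. Suppose an extra 10% to 30% of intervention residents receive 9 to 18 sessions at EUR 25 to 40 each.

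- Low: A = 0.10 × 9 × 25 = EUR 22.5 per resident.
- High: A = 0.30 × 18 × 40 = EUR 216 per resident.
- At E = 0.01: 22.5 / 0.01 = EUR 2,250 to 216 / 0.01 = EUR 21,600 per QALY.
- At E = 0.02: 22.5 / 0.02 = EUR 1,125 to 216 / 0.02 = EUR 10,800 per QALY.

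The high ends combine every extreme input. The example shows that a modest cost per resident can move a ratio when the QALY difference over six months is small. It is not an estimate for this trial.

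**The case against.** The strongest reply is that this is a condensed article. The list is not labelled exhaustive. Interview data are supplemented with use registered in the home, Table 1 mentions a resource-utilisation checklist (against hospital days) and medical-record registration, and the itemised form may well include therapist contacts. It is true that we cannot know what is on the form. But those are data sources, while the sentence at issue says which categories are costed, and it disagrees with the article's own account of the intervention. Medical aid could be stretched to cover therapy, but it reads more naturally as aids and devices; if therapy was meant, the text should say so.

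A second reply is that the psychotherapist consultation is programme delivery, not resident resource use. That is arguable, but the nursing home physician's consultation has the same status and is costed. The Discussion mentions only a nursing home physician for this consultation, and step 3 of the Intervention(s) section names no profession. That is an inconsistency with the abstract; it does not take the psychotherapist out of the abstract or out of step 2.

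Three stronger readings are tempting and are not supported:

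- A reader might infer that the care plans are stated to trigger physiotherapy, occupational therapy, dietetics or dental care. None is named as following from a plan. Table 2 is one resident's example and lists problems, not referrals. Nutrition is marked as observed only, dental health is not marked, and skin problems and falls may be managed by nurses or physicians. Use of other therapists is a reasonable inference from the rehabilitation, psychosocial and falls flags and from the other disciplines at the meeting, but no more than that.
- A reader might take the Process evaluation section to name therapists as those delivering the treatment. It says only that "physicians and therapists judgments about the intervention program and recommendations" are assessed. The participants it lists for interview are nurses, primary care physicians and nursing home physicians.
- A reader might conclude that all treatment induced by the model is counted as free. It is not: general practitioner, nursing home physician and specialist contacts, admissions, medication and aids are all in the list.

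**Conclusion.** The point holds in a limited form. The cost categories as printed omit therapist and allied-health contacts, although such care falls within the stated scope and a psychotherapist is a named part of the model. Followed as written, total costs value this care at zero in both arms.

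A bias in favour of the intervention requires higher use of such care in the intervention homes. That is plausible, since the model brings these disciplines into care planning, but the article does not say it. The size cannot be derived from the document, and the euro ranges above rest wholly on assumed uptake, session numbers, prices and QALY gains. The clinical outcome comparisons are not touched; the consequence is confined to the cost comparison, the cost-effectiveness and cost-utility ratios and the acceptability curves.

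**What to change.** Add one category to the list in the Economic evaluation section: contacts with the psychotherapist and with other therapists or allied-health professionals. Record it identically in both arms through the existing resource-use interview or checklist and the home and medical records. Value it by the Dutch costing guidelines already cited, and include it in the total costs used in the cost analysis and the cost-effectiveness analysis. If the category is left out on purpose, state why and name the omission as a limit of the total cost figure.

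The cost is a few extra checklist items and some additional record extraction. The cost result may turn out less favourable to the intervention.

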### Chronic disorders and homes for the elderly in the Netherlands

In our aging population the number of persons with a chronic disease is expected to increase from 1994–2015 with 25–60% [18]. In the Netherlands there are about 110.000 residents in homes for the elderly [4]. Professional care is needed for 71% of the residents such as assistance with activities of daily living or mobility, nursing care (medication, wound care etc) and domestic help. Twelve percent of persons of 75 years and older live in a home for the elderly and 4% in a nursing home [19]

The quality of care in these homes is frequently discussed in national and international newspapers. The care organizations responsible for the quality of care given in homes for the elderly often do not have the tools to measure and improve quality of care. Scientific studies of quality of care for the elderly are rare.

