#### Secondary outcome measures are

4. Care satisfaction of residents is measured by the brief QUOTE, which wording was slightly adapted to fit the institutional setting [33].

5. ADL and IADL disability is measured by GARS [34].

6. (Days until) placement in a nursing home is surveyed and crosschecked at institutes.

7. (Acute) hospitalization is surveyed and cross-checked at the local hospital which covers 95% of all admissions in the region.

8. (Days until) mortality is checked in the administration of the homes.

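### The stated cost categories omit residence and staff care in the home for the elderly but include nursing-home medical-department admissions, so shifts between the two settings are costed on one side only

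*Protocol article*

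**What the plan says.** Under Economic evaluation, cost data come from resident interviews at baseline and 6 months, "from a societal perspective and supplemented with resource use as registered within the home for the elderly". The scope is then narrowed: "Only direct healthcare costs will be considered, because all patients have retired". The categories follow: "Included cost categories are costs of consultations with the general practitioner, the nursing home physician and medical specialists, hospitalizations and admissions to the medical department" and, in the same sentence, "of the nursing home and use of medication and medical aid". On prices the section says only: "Care consumption will be valued according to guidelines for economic evaluation in health care in the Netherlands".

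Under Cost effectiveness analysis, "the difference in total costs between the intervention and usual care group are compared with" the difference in functional health and disability. A cost-utility analysis is added, in which QALYs are utility multiplied by time spent in the health state. The Cost analysis section bootstraps the difference in mean costs.

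The Background describes the setting: "Professional care is needed for 71% of the residents such as assistance with activities of daily living or mobility, nursing care", together with domestic help. Time to nursing-home placement and time to death are secondary outcomes. Table 1 takes both from the home's registration. For direct costs it names interview, pharmacy and medical records.

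**The concern.** The list includes one setting in which a resident may receive care, the nursing-home medical department, but not the setting that such a stay may replace. The reason given for the narrowed scope is retirement, which explains leaving out productivity costs. It does not explain leaving out nursing and personal care by the home's staff, which is care delivered to the resident and falls inside the article's own restriction to direct healthcare.

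A cost common to both arms would cancel in the difference. This one need not. Placement and mortality are outcomes the trial expects it may change. The intervention also identifies care needs and writes care plans, so it may change how much staff care is given. If any of these differs by arm, the omitted cost differs too. The error then passes into the cost difference, its bootstrap interval, the cost per QALY and the acceptability curves. Resampling measures the sampling variation of the costs that were counted and cannot restore one that was not.

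**Working it through.** The article gives no unit price and no expected cost difference, so it has no figure of its own to reproduce on this point. The check is a reading of the list, followed by simple cost accounting.

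**Step 1: the list, item by item.**

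- Present: consultations with the general practitioner, nursing home physician and specialists; hospital stays; nursing-home medical-department admissions; medication; medical aids.
- Absent: residence in the home for the elderly; nursing and personal care by its staff.
- Unclear: what the use registered within the home covers. No listed category corresponds to staff care, but the sentence could feed physician visits or aids, which are listed.

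**Step 2: what each event is credited with.** Let N be the price of a nursing-home day, H the price of a home day (residence plus staff care), and M the listed medical costs of a day at home. For clarity, M is set aside in the first three rows.

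| Event | True change in cost | Change under the listed categories | Error |
|---|---|---|---|
| Medical-department day averted; home place would have been given up | −(N − H) | −N | saving overstated by H |
| Medical-department day averted; home place would have been kept and still charged | −N | −N | none |
| Day averted in another nursing-home department; home place would have been given up | −(N − H) | 0 | saving of N − H missed |
| One more day alive in the home | H + M | M | H missed |

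The first and last rows favour the intervention if it delays placement or prolongs survival. The third works against it when N exceeds H. All reverse if the assessments speed up placement or survival is shorter.

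**Step 3: size for the first row.** With q = H/N (assumed; range 0.3 to 0.6), overstatement = N/(N − H) = 1/(1 − q):

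- q = 0.3: 1/0.7 = 1.43
- q = 0.4: 1/0.6 = 1.67
- q = 0.5: 1/0.5 = 2.0
- q = 0.6: 1/0.4 = 2.5

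This factor applies to that component alone, not to total cost.

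**Step 4: size for survival.** Follow-up is six months, about 182.5 days. Assume an absolute mortality difference d at 6 months, deaths spread evenly over the period, and the gained days spent in the home. Extra home days per randomized resident = d × 182.5/2:

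- d = 0.01: 0.91 days
- d = 0.02: 1.8 days
- d = 0.05: 4.56 days

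At an assumed 60 to 150 euro per home day, the uncosted amount runs from 0.91 × 60 = 55 euro to 4.56 × 150 = 684 euro per randomized resident.

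**The case against.** The strongest reply is that the article condenses a fuller protocol, does not call its list exhaustive, and mentions use registered within the home, so staff care may be collected and valued. This stands in part: a reader might infer that the list is closed and in-home care is certainly uncosted, and the text does not prove that. But the article does state its categories, and none of them is staff care or residence. The two sentences have to be reconciled.

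A reader might also infer that longer survival costs nothing in this analysis. That is too strong, because the listed consultations, hospital stays, medication and aids still accrue.

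A third tempting inference is that the omission favours the intervention. The documents do not support a direction. The listed item covers the medical department only, the article does not equate it with permanent placement, and placements elsewhere are not listed at all. Where the home place is kept during an admission, no offset for residence is due.

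Finally, accommodation may be said to fall outside direct healthcare. That is arguable, and the societal label leaves the scope unclear. It does not cover nursing and personal care. If the nursing-home day price includes bed and board, leaving them out on the home side alone is inconsistent.

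**Conclusion.** The point holds as an asymmetry in the stated categories, and it should be corrected before costs are analysed. Neither its net direction nor its size can be determined from the article. The factor of 1.4 to 2.5 rests on an assumed price ratio and applies only to averted medical-department days for which the home place would have been given up. The 0.9 to 4.6 days rest on an assumed mortality difference of 1 to 5 points with evenly spread deaths. The euro range adds assumed prices to that. Residence time common to both arms cancels and is not at issue.

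**What to change.** In the Economic evaluation section, add a category for both arms: days resident in the home for the elderly, including nursing and personal care. Count it from baseline to death, permanent nursing-home placement or 6 months, whichever comes first. Value it per day under the Dutch guidelines already cited, and carry it into the totals used under Cost analysis and Cost effectiveness analysis.

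Three statements should go with it:

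- The use registered within the home feeds this category where it records staff care. If it does not, acknowledge that a flat day price cannot capture changes in care intensity, so extra care prompted by the care plans stays uncosted.
- Accommodation is treated by the same rule in the home and in the nursing home.
- Which nursing-home stays the listed admission item covers. Otherwise, for a placement elsewhere, home days would stop and no nursing-home cost would start.

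Placement and death dates are already collected, so residence days need no new resident data. Capturing care intensity depends on what the homes record and may take more work. The statistical cost is one more component and a somewhat larger variance of total costs.
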